### Sample size considerations

Based on the most recent meta-analysis, we expect a pain response in 60% of patients following standard radiotherapy [3]. Pain response after stereotactic radiotherapy is assumed to be 85% [8, 9]. We expect that approximately 90% of patients who are offered SBRT treatment, will accept the offer. Cross-over from control arm to the SBRT treatment arm is extremely unlikely, since only patients who are randomly selected to receive SBRT are informed about the treatment. Taking a one-sided α of 5% and a power of 80%, we require 49 patients per treatment arm to show a statistically significant difference of 15% in pain response. The reason to choose a one sided α is that, although improbable, inferior pain response after stereotactic treatment would lead to the same action as no difference at all between the two treatment regimen. This is because the SBRT treatment will only be implemented if it is significantly better than the usual care, since SBRT treatment is more complex, less convenient for patients, and more expensive than standard radiotherapy. Finally, to allow for a 10% drop out rate, recruitment of 55 patients per group is intended. We expect to complete recruitment within 18 months based on the number of patients we treat in our center annually.

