### Data analysis

Data will be analyzed according to the intention to treat principle. Data of eligible patients who were randomly offered stereotactic radiotherapy will be compared with eligible patients who were not randomly selected and received standard radiotherapy. In case of dropout (i.e. patients not surviving longer than three months or patients unable to provide pain scores and analgesic use), a worst-case analysis will be performed: dropped-out patients will be classified as non-responders. In case of substantial refusal of the SBRT offer in the intervention arm, instrumental variable analysis will be used to account for non-compliance [26]. The primary outcome (i.e. proportion of patients with response to radiotherapy) will be presented in absolute numbers and proportions. Differences in pain response will be compared by χ2 test. If randomization fails, imbalances between baseline characteristics will be adjusted by logistic regression analysis. Differences in duration of response and overall survival will be analysed by Kaplan-Meier analysis and log rank test. Toxicity will be presented as the overall incidence of grade 3–4 toxicity and incidence of vertebral compression fractures. Differences will be tested with the χ2 test. A comparison in QOL will be made between the baseline QOL and at predefined intervals after treatment. A change of 10% of the scale breadth will be considered a clinically relevant change of QOL [27]. Data will be presented as improved (≥10% increase), stable, or worsened (≥10% decrease) QOL. We will evaluate the pattern of QOL as a continuous outcome over time using mixed models. Differences with a *P*-value <0.05 will be considered statistically significant. We have planned to perform an interim analysis after inclusion of half of the patients (i.e. 55 patients) when they have completed their follow up (i.e. three months pain assessment).

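### The planned interim at 55 patients is not exempted from the general P<0.05 rule; if it is a one-sided efficacy look, type I error would be about 8% instead of the declared 5%

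*Protocol article*

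**What the plan says.** All the relevant text is in the protocol article.

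- **Interim.** The last sentence of Data analysis reads: "We have planned to perform an interim analysis after inclusion of half of the patients". It gives the number as 55 and times the analysis to when these patients have their three-month pain assessment. Under Primary endpoint, the primary outcome is complete or partial pain response at three months.
- **Threshold.** The sentence just before it sets the only threshold in the article: a P-"value <0.05 will be considered statistically significant". It makes no distinction between interim and final analysis. The primary comparison is a χ2 test, and Data analysis does not say whether its P-value is one- or two-sided.
- **Design alpha.** Sample size considerations states: "Taking a one-sided α of 5% and a power of 80%, we require 49 patients per treatment arm". The reason given for a one-sided test is that an inferior SBRT result would lead to the same action as no difference.

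The article gives no purpose, tested endpoint, stopping rule or boundary for the interim.

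**The concern.** The interim is triggered by the maturity of primary-endpoint data, and the one threshold on the page covers every comparison without exception. Taken literally, pain response could be tested at 55 patients and again at 110, each time at the full level. Two chances to cross the same limit give a larger false-positive probability than one, so the declared 5% would not hold.

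This matters because of the sponsor's own reasoning. Sample size considerations says SBRT will be adopted only if significantly better than usual care, since it is more complex, less convenient and more expensive. Control of false superiority claims is therefore the criterion on which the design rests. A positive claim at half the sample would also tend to overstate the benefit, because only large observed differences cross the limit at that size.

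**Working it through.** **1. Reproduce the planned sample size.** Inputs from Sample size considerations: control response 60%, SBRT response 85%, acceptance 90%, one-sided alpha 5%, power 80%.

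- Intention-to-treat response in the offered arm: 0.9 × 85% + 0.1 × 60% = 82.5%, a difference of 22.5 points.
- n per arm = [z(0.95)·√(2·p̄·(1−p̄)) + z(0.80)·√(p1(1−p1) + p2(1−p2))]² / (p2−p1)², with p̄ = 0.7125.
- = [1.645 × √0.4097 + 0.842 × √0.3844]² / 0.225² = 48.98, so 49. With 10% dropout, 49/0.9 gives 55.

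The stated 49 and 55 are reproduced with the whole one-sided 5% at a single final test. (The 15% difference named in the same sentence does not match these rates; that is a separate matter.)

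**2. Error with two looks at the stated threshold.** The information fraction is 55/110 = 0.5, so under the null the two z-statistics have correlation √0.5 = 0.707. For limits c1 and c2:

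P(reject at either look) = P(Z1>c1) + P(Z2>c2) − P(Z1>c1 and Z2>c2)

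| Rule at interim, then final | Calculation | Error favouring SBRT |
|---|---|---|
| One-sided 5% at both (1.645) | 0.0500 + 0.0500 − 0.0199 | 8.0% |
| Two-sided 5% at both (1.96), upper side | 0.0250 + 0.0250 − 0.0084 | 4.2% |
| One-sided 0.001, then one-sided 5% | 0.0010 + 0.0500 − 0.0008 | 5.02% |
| No efficacy claim at interim, final one-sided 5% | 0.0500 | 5.0% |

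A simulation of the binary endpoint (response 60% in both arms, 27 and 28 patients at the interim, 55 per arm at the end, 2 million runs) gives 8.1% for the first row.

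**3. Overstatement and chance of an early claim.** Assume the planned rates (60% and 82.5%) and 27 and 28 patients at the interim.

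- Standard error under the null: √(0.7145 × 0.2855 × (1/27 + 1/28)) = 0.122.
- Standard error under the alternative: √(0.24/27 + 0.1444/28) = 0.119.
- Chance of crossing one-sided 5%: Φ((0.225 − 1.645 × 0.122)/0.119), about 58%.
- Chance of crossing one-sided 0.001: Φ((0.225 − 3.09 × 0.122)/0.119), about 10%.

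Simulation gives 59% for the first. The mean observed difference in those runs is about 30 points, against a true 22.5.

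**The case against.** The strongest objection is that the article gives the interim one sentence, and that purpose, boundary and decision rule commonly sit in a full protocol or analysis plan, which are not shown. Their absence is not in itself an error, and that stands. What remains is a stated rule: P<0.05, unqualified, directly before a stated interim tied to the primary-endpoint time point.

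Several stronger readings are tempting, and the document does not support them.

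- **That type I error does rise to 8%.** This needs a between-arm comparison of pain response at the interim, at one-sided 0.05, with an early claim allowed. The article states none of these. The P<0.05 sentence can be read as a general convention for the listed analyses.
- **That the interim is unblinded by arm.** The article does not say who sees the interim data or whether arms are compared.
- **That 8.3% (8.6% by simulation), the figure for two-sided 5% at both looks, is the risk of a false superiority claim.** It counts rejections in both directions. In favour of SBRT the figure is 4.2%, below the declared one-sided 5%.
- **That sizing at the full 5% shows a defect.** It does not. A trial with a strict interim limit such as Haybittle-Peto would have the same sample size.

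The overstatement of effect is likewise conditional on an early claim being made.

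**Conclusion.** The point holds in conditional form. The text sets a single P<0.05 threshold, does not exempt an interim timed on primary-endpoint data, and declares a one-sided alpha of 5%. If pain response is compared at the interim at one-sided 0.05 and a positive result can be claimed, the declared 5% becomes about 8.0%. That figure assumes one interim at half the information and the usual joint normal approximation. If the P-value is two-sided, or the interim serves only futility or safety, the declared level is not exceeded. The article does not settle which case applies, and a threshold chosen after the interim data are seen could not restore error control. It should be fixed, but it is not proof that the trial's error rate is inflated.

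**What to change.** Before interim data are seen, add one sentence to Data analysis that takes the interim out of the general P<0.05 rule, in one of two ways:

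1. Efficacy may be claimed at the interim only at one-sided P<0.001 (Haybittle-Peto), and the final χ2 comparison is tested at one-sided 5%. The overall error is 5.02%.
2. The interim makes no between-arm comparison of pain response. The final test keeps the whole 5%.

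The sample size is unchanged under either. Under the first, final power is not reduced, because the final limit stays where the sample size calculation put it. The cost is that an early efficacy claim becomes harder: at the planned rates, the chance of one at the interim falls from about 58% to about 10%. Under the second there is no early efficacy claim.

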## Discussion

In this report, we present the rationale and design of the VERTICAL trial. In this randomized study, we investigate whether SBRT can increase the proportion of patients with (complete or partial) pain response. Although standard radiotherapy is moderately effective in achieving pain relief in most patients with spinal metastases, up to 40% of patients do not experience any pain relief and complete response occurs in only 30% of responders [3]. Presently, it is not exactly understood why some patients do not respond (adequately) to standard radiotherapy. A factor that may play a role in the suboptimal response to standard radiotherapy is the way the radiation dose is delivered. Barton and colleagues [28] showed that the dose received by the vertebral column using standard radiation techniques varies by up to 50%. For instance, when using a direct posteroanterior field to deliver 8 Gy at a depth of 5 cm, metastases located in deep vertebrae receive less than 50% of the prescribed dose. This is important, since 4 Gy in one fractions is proven to be less effective than 8 Gy [29–31]. If there is indeed a threshold dose below which pain relief is less likely and of slower onset, it may be important to ensure that the vertebral metastasis receives the dose intended. However, the low tolerance of the spinal cord to radiation limits the standard radiation dose to a level that below the optimal therapeutic dose thus providing a less than optimal response. Precise confinement of the radiation dose, even including dose escalation in addition, should increase the probability of pain relief while the risk of injury to the spinal cord is minimized. Several retrospective and prospective phase II studies have indeed shown the safety and efficacy of SBRT in spinal metastases [5, 6].

Most studies on spinal SBRT included a heterogeneous patient population, including previously unirradiated patients, patients who needed reirradiation, and post-operative SBRT, and these categories include patients with or without solitary spine metastases [8, 32]. We include all unirradiated patients with spinal metastases including patients with diffuse metastases, and mild neurological complaints. In this way, we deliberately chose a pragmatic approach since we expect that this would be the patient population that is going to be treated once the benefits of SBRT would have been established. In order to investigate the effect of SBRT without the effect of additional treatments, we however exclude patients who received previous standard or stereotactic body radiotherapy or surgery to the index site. As pragmatic trials investigate the effectiveness of medical treatment strategies under usual conditions, the standard strategy (i.e. 8 Gy in a single fraction, or for selected patients 30 Gy in 10 fractions) will be compared to the SBRT strategy (which includes more dose schedules). Still, the biological effective dose (BED) of the three dose regimen is much higher compared to the BED of the conventional dose regimen. If there is a difference in pain response after SBRT compared to standard radiotherapy, we should be able to detect that differences despite the use of multiple radiation dose schedules. Traditionally, stereotactic radiotherapy in metastatic bone disease is intended for patients with spinal metastases. However, SBRT is increasing being applied in the treatment of non-spine osseous metastases [33]. Since spinal metastases are similar to non-spine osseous metastases in terms of bone involvement and pain relief after standard radiotherapy [34, 35], the response after SBRT in spinal and non-spine osseous metastases is likely to be similar as well. Therefore, we have extended the VERTICAL inclusion criteria to patients with non-spinal bony metastatic disease.

To our knowledge, six other randomized studies on spinal SBRT are currently being conducted (Table 3) [36–41]. Only two other trials require both CT and MRI imaging for the delineation of the spinal metastases [37, 38], however, these trials delineate the whole bony compartment (i.e. the CTV) that contains the metastasis instead of using an simultaneous integrated boost approach. They also have strict instructions on how to apply the standard and stereotactic body radiotherapy in contrast to our more pragmatic approach, offering radiation oncologists leeway in fractionation schedule. Furthermore, the VERTICAL trial distinguishes itself from these trials by applying the cmRCT design. The cmRCT design was proposed as a variant of classic pragmatic randomized controlled trials (RCTs) and addresses some common difficulties associated with those RCTs, such as disappointment bias, drop-outs, slow recruitment, and poor generalizability [13]. Patients and doctors often have a strong preference for the experimental treatment that has not proven to, but is expected to be superior. Investigators of the RTOG 0631 trial indeed experience that patients and their physicians prefer the SBRT treatment over standard radiotherapy [[name], personal communication]. Consequently, patients allocated to the standard arm may show disappointment when reporting outcomes. This is of particular concern since the primary endpoint consists of a subjective outcome (i.e. pain scores). By using the cmRCT design however, control patients are unaware of being allocated to the control arm, which will prevent disappointment bias in observed outcomes. Furthermore, standard of care is likely to be unaffected by treatment allocation and will therefore better resemble routine practice. We also expect lower drop-outs rates since patients in the control arm are not likely to withdraw from standard care, which may be of particular interest in this fragile patient population. Because of this fragility, researchers in this field should make an effort to optimize recruitment rates. The use of the cmRCT design may foster recruitment rates by its unique informed consent procedure. A reason not to take part in classic randomized studies might be that patients cannot be guaranteed to receive the desired experimental treatment. Furthermore, once participating, patients are often allowed to participate in one trial at a time only. By contrast, patients participating in a cmRCT study give broad informed consent to participate in randomized trials, but not to specific trials which may increase recruitment rates. Moreover, the cmRCT cohort offers an infrastructure which allows the conduct of randomized trials simultaneously. Finally, recruitment in cohort studies is usually more manageable compared with recruitment in RCTs. The inclusion rates in the PRESENT cohort for example are promising: the participation rate is 83%, and 88% of the participating patients have given informed consent for broad randomization to experimental interventions. The use of a cohort in cmRCT studies offers more potential advantages. Palliative patients willing to participate in randomized trials often represent a relatively healthier and higher-educated subgroup. By using a cohort as a recruitment pool for RCTs, a more routine population is included since recruitment for cohort studies is generally less selective. Moreover, the cohort provides information on baseline characteristics and outcome measurements (i.e. the regular cohort measures) of drop-outs, which is essential in the data analysis. Patients allocated to the control arm, are cohort participants who receive the current standard of care (i.e. standard radiotherapy in the PRESENT case). In our department, the standard of care for patients with bone metastases will change from standard radiotherapy to automatically generated conformal treatment plans. Would the VERTICAL trial have been conventionally conducted, this could have been problematic since control patients in the VERTICAL trial would then have been withhold from standard of care. However, the cmRCT design has the advantage that experimental interventions are compared with the most up-to-date standard of care, instead of competing with outdated treatments, which is often the case in completed classic RCTs. Finally, a valuable feature of the cmRCT design is the opportunity to evaluate and quantify the acceptance rates of the offered treatment (i.e. SBRT). This offers new insights into patient preferences and reasons for refusal of SBRT. We feel that prevention of disappointment bias, more efficient and less selective patient recruitment, up-to-date standard of care, and quantifying patients’ preference could significantly improve trials conducted according to the cmRCT design.

**Table 3 Tab3:** Randomized trials on SBRT for spinal metastases^a^

Name, institution	Start date, sample size	Patients	SBRT treatment	Comparator	Primary Endpoint
Mahadevan et al. [36] Beth Israel Deaconess MC	01–2012 81	Number of sites not stated; Pain ≥ 5; No rapid neurologic decline	Total dose unknown in 1, 3, or 5 fractions; No more information provided	Standard EBRT in 10 fractions	Pain response^b^
RACOST [37] Radboud UMC Nijmegen	06–2015 382	Number of sites not stated; May have other visceral metastases; Pain ≥ 5; No neurologic deficit	Any modern system; 20 Gy in one fraction; Delineation with MRI and CT; Target volume is GTV, with bony CTV expansion, PTV margin ≤ 3 mm	Standard EBRT single dose of 8 Gy, no restrictions to radiation technique	Pain response taking administration of opioids into account^b^
RTOG 0631 [38] Henry Ford Hospital	11–2011 395	Up to 3 spinal sites; May have other visceral metastases; Pain ≥ 5; No rapid neurologic decline	IMRT or other dose painting technique; 16 or 18 Gy in one fraction; Delineation with MRI and CT; Target volume is involved VB	Standaard EBRT single dose of 8 Gy, 2D and 3D conformal therapy	Pain response (increase or decrease of ≥ 3 points) at 3 months
SMART [39] Heidelberg University	12–2014 60	Up to 2 spinal sites; No neurologic deficit	IMRT; 24 Gy in one fraction; Delineation with CT; Target volume is involved VB with PTV margin	Standard EBRT 30 Gy in 10 fractions, 3D conformal planning	Pain response (increase or decrease of > 2 points) at 3 months
SPIN-MET [40] University of Erlangen-Nürnberg	03–2013 155	Number of sites not stated; May have other visceral metastases; No rapid neurologic decline	36 Gy in 12 fractions plus integrated boost 48 Gy in 12 fractions; No more information provided	Conventional EBRT 30 Gy in 10 fractions	Tumor control defined as time to progression on MRI
Tingting et al. [41] Cancer Hospital of Shantou UMC	03–2014 100	Up to 3 spinal sites	24 Gy in 2 fractions; No more information provided	Conventional EBRT 30 Gy in 10 fractions	Pain response taking administration of opioid into account^b^
VERTICAL University Medical Center Utrecht	01–2015 110	Up to 2 spinal sites; May have other visceral metastases; Pain ≥ 3; no rapid neurologic decline	VMAT; 18 Gy in one fraction or fractionated equivalent; Delineation with MRI and CT; Target volume with simultaneous integrated boost	Standard of care for standard radiotherapy	Pain response (increase or decrease of ≥ 2 points) taking administration of opioid into account at 3 months

*CT* computed tomography, *CTV* clinical target volume, *EBRT* external beam radiotherapy, *IMRT* image guided radiotherapy, *GTV* gross tumor volume, *MC* medical center, *MRI* magnetic resonance imaging, *PTV* planning target volume, *VB* vertebral body

^a^Excluding studies on oligometastases including spinal oligometastatic disease, comparing surgery with SBRT, and studies including non-spinal lesions as well

^b^Time point at which endpoint is measured not given

In conclusion, the VERTICAL study is a pragmatic randomized trial, following the cmRCT design, which compares stereotactic radiotherapy with standard radiotherapy in patients with spinal metastases in terms of pain response, with the ultimate goal to improve quality of life.

## Abbreviations

BED: Biological effective dose
BPI: Brief pain inventory
CBCT: Cone beam computed tomography
cmRCT: Cohort multiple randomized controlled trial design
CT: Computed tomography
CTV: Clinical tumor volume
EORTC: European organization for research and treatment of cancer
GTV: Gross tumor volume
Gy: Gray
IMRT: Intensity-modulated radiation therapy
KPS: Karnofsky performance score
MRI: Magnetic resonance imaging
MV: Megavoltage
OAR: Organs at risk
PRESENT: Prospective evaluation of interventional StudiEs on boNe meTastases cohort
PROFILES: Patient reported outcomes following initial treatment and long term evaluation of survivorship
PROMs: Patient-reported outcomes
QOL: Quality of life
RCT: Randomized controlled trial
SAE: Serious adverse event
SBRT: Stereotactic body radiotherapy
VERTICAL: Comparison of conVEntional RadioTherapy with stereotactIC body radiotherapy in patients with spinAL metastases
VMAT: Volumetric modulated arc therapy
